### Analysis and Statistical Methods

Semi-structured interview and focus group transcripts will be coded according to content and common themes regarding acceptability and feasibility will be identified.

Quantitative measures of acceptability will be presented as descriptive statistics.

The outcomes between the three arms of the study will be compared using statistical tests on adequately powered measures. Descriptive statistics (mean, SD and 95% CI) will be presented on underpowered measures.

Multilevel modelling based on the Piasecki model of cigarette withdrawal [33] will be used to investigate the effects of the dietary interventions on urges to smoke during the first 4 weeks of quitting. We will investigate whether these effects are mediated by hunger/food craving score (HCS) and ketosis. We will adjust for confounding variables e.g. active treatment for depression. Analysis will be carried out on all those who continued to try to quit regardless of lapses to smoking and this will be adjusted for in the model as described above.

Significance is set at the 5% level, exact p values will be given and 95% confidence intervals where appropriate.

Analysis of data from treatment stage 1 will be undertaken once every participant has completed this stage. Analysis from treatment stage 2 and follow-up at 6 months and one year will be undertaken once participants have gone through each of these phases.

### Data Validation

Data cleaning will take place by a series of logical checks on the electronic data. (For example, a person cannot be recorded as prolonged abstinent smoker at 6 months if they were not in such a state at 8 weeks). Discrepant records are checked with the source documents and the database amended if necessary.

### Trial schedule

One Doctoral researcher is principal investigator and supervising dietitian. Part-time support is provided by practice research nurses and research administrators.

Recruiting will continue over a period of a year until sufficient participants have been treated in each trial arm. Follow up will take place as described and it is estimated that the trial will be complete 2 years from the start.

### Definition of end of trial

End of trial is defined as the final 12 month follow-up where the last measurement is taken from the last participant and the last participant undergoing the trial is debriefed.

### Value of Results

The results from this study will provide new information about dieting during smoking cessation. They will inform the design of a multi-component intervention that tackles both smoking cessation and its related weight gain in a way which can be rolled out into the NHS.

### Assessment of safety

Potential participants' safety is ensured by screening for eligibility using a structured form completed by the trial healthcare professionals. This will record evidence of eligibility and that the person does not have any exclusion criteria. In addition, the nurse will take a general medical and drug history to assess for other complicating diseases. Any queries remaining as a result of this process are resolved by discussion between the trial nurse, chief investigator and the relevant physicians providing routine medical care, usually the participant's GP. Such concerns are unusual but not rare. Typically, they arise from a participant's hazy knowledge or understanding of their past medical history and are usually readily resolved. No blood or further medical testing is necessary to ensure safety.

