#### Exclusion Criteria

• Any of the absolute or relative contraindications to VLCD use. These include situations in which rapid weight loss would be unsafe: pregnancy, breastfeeding, myocardial infarction/unstable angina/acute coronary syndrome in the past 6 months, cerebrovascular accident/transient ischaemic attack/stroke in the past 3 months, major surgery in the last 3 months, severe cardiac arrhythmias, severe hepatic impairment, severe renal impairment (i.e. GFR ≤ 29 mls/min), active carcinoma, untreated gallstones, past history of anorexia nervosa or bulimia nervosa, type 1 diabetes, those aged over 70 years with a BMI < 30. A large energy deficit alters metabolic rate and so anyone with unstable thyroid function is also excluded. Sudden weight loss may cause fainting or precipitate gout in those who are susceptible so those with regular blackouts or fainting, and untreated gout are also excluded. The VLCD formula is made from milk so is unsuitable for anyone with a milk allergy or intolerance.

• Uncontrolled hypertension and type 2 diabetes treated with medication. Although these are not contraindications to the VLCD they are excluded as adjusting the medications in these conditions would require specialist advice beyond the scope of the research nurses in this trial (diet controlled type 2 diabetics may be included).

• Those on oral anticoagulants, digoxin, phenytoin and lithium are excluded due to likelihood of increased drug absorption if on a VLCD. Specialist advice beyond the scope of our research nurses is needed to reduce and monitor these medications.

• Those on diuretics for diuresis are excluded as a VLCD can potentiate diuresis and increase the risk of hypokalaemia. Those on low dose diuretics for treatment of hypertension are not excluded as the risk is of hypokalaemic complications on these are low [20,21]. The effects of combining a VLCD with low dose thiazides has not been well studied and may be unpredictable therefore serum potassium will be monitored weekly and the VLCD discontinued if levels fall below 3.1 mmol/l. (Additional file 2 contains full list of excluded medications).

• Previous severe adverse reaction to nicotine patches (that which precludes further use).

• Active phaeocromocytoma as this combined with use of NRT may increase the risk of hypertension and tachycardia.

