#### Measurement of Disease Risk Factors

These are measured as described below. The schedule of measurements is contained in table 2.

**Table 2 T2:** Measurements to be taken at each point in trial

Treatment week	-2	-1	0	1	2	3	4	5-7	8-10		12	26	52
Baseline Questionnaire (with Fagerstrom Score) 7 day food diary		√											

Weight		√	√	√	√	√	√	√	√	√	√	√	√

Waist/Hip ratio		√	√	√	√	√	√	√	√	√	√	√	√

BP/HR		√	√	√	√	√	√	√	√	√	√	√	√

Smoking Status		√	√	√	√	√	√	√	√	√	√	√	√

Urinary ketones		√	√	√	√	√	√						

Fasting Blood test	√										√	√	√

Lung function	√										√	√	√

Russell Standard									√		√	√	√

QOL measure		√					√				√		

Confidence in trial arm	√						√				√		

Percentage Body Fat composition		√	√	√	√	√	√	√	√	√	√	√	√

Daily Diaries		√	√	√	√	√	√						

Weekly Diaries								√	√	√	√	√	√

HCI		√									√	√	√

1. Weekly weight, waist to hip ratio, % body fat composition, blood pressure, and heart rate.

2. FEV1 and FVC post 200 mg salbutamol as is recommended by the American Thoracic Society 2005 standards for measuring lung function [35] at baseline, 3, 6 and 12 months.

3. Fasting blood glucose, Total cholesterol (TC), low density lipoprotein (LDL) cholesterol, high density lipoprotein (HDL) cholesterol TC/HDL ratio, triglycerides, haemoglobin, white blood cell count, platelet count, mean cell volume and c-reactive protein (CRP).

Full details of how these measurements are taken are contained within the trial clinical protocol as standard operating procedures (SOPs) and work instructions (WIs). The nurses are trained in these procedures so that they are carried out consistently at each trial site. The nurses are assessed in practice against these SOPs and WIs, every couple of months, by the principal investigator.

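### Severe renal impairment is excluded by a GFR cut-off, yet the article says no blood testing is needed and describes no screening step that supplies a GFR (minor, individual safety only)

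*Protocol article*

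**What the plan says.** Under Exclusion Criteria, the protocol article lists contraindications to the VLCD, described as including "situations in which rapid weight loss would be unsafe". One of them is "severe renal impairment (i.e. GFR ≤ 29 mls/min". It is the only exclusion in that section given a laboratory threshold.

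Under Assessment of safety, screening has three parts. A structured form is to document eligibility and the absence of every exclusion. The nurse takes a medical and medication history. Then: "Any queries remaining as a result of this process are resolved by discussion between the trial nurse, chief investigator and the relevant physicians", who are usually the participant's GP. The section says such queries typically come from a participant's "hazy knowledge or understanding of their past medical history". It closes with "No blood or further medical testing is necessary to ensure safety".

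Under Measurement of Disease Risk Factors, item 3 gives the fasting panel: glucose, lipids, and then "haemoglobin, white blood cell count, platelet count, mean cell volume and c-reactive protein (CRP". Item 1 gives the weekly measures: "Weekly weight, waist to hip ratio, % body fat composition, blood pressure, and heart rate". Table 2 has a row for "Fasting Blood test", marked, as the table reads in the available text, at weeks -2, 12, 26 and 52.

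**The concern.** An exclusion set at a laboratory value can be applied reliably only if someone has the value. Here the cut-off is explicit, and so is the statement that blood testing is unnecessary. The point therefore concerns what the article states, and not only a detail left out for brevity.

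The physician is consulted when a query remains. A person who knows of kidney disease, or whose history suggests it, should raise one. A person whose impairment has never been recognised has nothing to report and may raise none. If that person is allocated to the VLCD, they receive for 5 weeks a diet that the protocol's own criteria treat as unsafe for them. What is at stake is the safety of that individual.

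**Working it through.** No figure in the plan needs reproducing. The check is whether anything described supplies the value that the criterion needs.

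1. **Value needed:** a GFR, to be compared with 29 mls/min (Exclusion Criteria).
2. **Screening steps** (Assessment of safety):
   - Form: must record evidence that no exclusion applies, but the source of evidence for renal function is not stated.
   - History: gives known disease and current medicines, not a GFR.
   - Physician contact: could give a recorded GFR, but is described only for queries that remain.
3. **Blood tests** (Measurement of Disease Risk Factors; Exclusion Criteria):
   - The fasting panel covers glucose, lipids, blood count and CRP. It lists no creatinine, urea or eGFR.
   - The only other blood test is weekly serum potassium, tied to low-dose diuretic use. It monitors treatment and does not screen for renal impairment.
   - The weekly measures are not tests of renal function.
4. **Exposure:** the VLCD runs for 1 week before quitting and 4 weeks after, so 1 + 4 = 5 weeks. Only the VLCD arm receives it. Sample Size plans 30 per group, with an aim of 42.
5. **Is blood available in time?** Table 2, as it reads, puts the first fasting sample at week -2, and Treatment Stage 1 starts the diets at week -1. That is 1 week before the diet.
6. **Is it available before allocation?** This is less clear. Treatment Stage 1 puts baseline at week -3. Randomisation has the clinician reveal the allocation at week -3, but also says the function is locked until all week -2 data are complete. If allocation is at week -3, a week -2 result comes after it. Acting on that result only in people about to start the VLCD would then remove people from one arm. Any check must therefore come before randomisation and apply to all arms.

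Steps 2 and 3 together: nothing described is required to produce a GFR, although the form and the GP contact could.

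**The case against.** The strongest reply is that the article condenses a fuller clinical protocol. The form must document that no exclusion applies, and which field or source it uses is form-level detail. Clinics are held in GP practices and invitations come from the person's own GP, so a recorded eGFR may be at hand. The sentence on blood testing does not forbid looking one up. The GFR figure can also be read as explaining what severe means. Other exclusions in the list, such as severe hepatic impairment or untreated gallstones, could equally go unrecognised, and no test is required for them.

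There are also safeguards during treatment: withdrawal if a contraindication emerges, weekly clinical review with a supervising GP, a VLCD side-effect checklist with escalation, and weekly reporting of intercurrent illness.

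Most of this stands, and it keeps the point small. It does not close the gap. None of the safeguards is described as measuring renal function, and record access helps only if someone is told to look. Renal function differs from the other exclusions named because the investigators gave it a laboratory value.

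A reader might infer three stronger things that the document does not support:

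- **That people with known renal impairment would be enrolled.** The form, the history and the GP contact are there to catch them.
- **That the sentence contradicts the weekly potassium rule.** It closes a paragraph on eligibility screening, while the potassium rule concerns people already on the diet.
- **That the fasting panel is a failed safety screen.** It is listed to measure disease risk factors and is not presented as an eligibility test.

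**Conclusion.** The point holds in a limited form. The article sets a laboratory-defined exclusion, says that no blood testing is needed, and describes no step that must supply the value. A rare unrecognised case could be randomised and given the VLCD.

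It is a minor matter of individual safety. The document gives no basis for estimating the frequency, and at most the 30 to 42 people planned for the VLCD arm are exposed. The comparisons between arms and the trial's conclusions are unaffected.

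The conclusion assumes that the unseen form does not already require a recent eGFR. If it does, only the wording of the sentence needs attention.

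**What to change.** For all participants, before randomisation, require a recent eGFR on the eligibility form, with the investigators setting how recent. Take it from the GP record. Where none exists, add creatinine to the baseline fasting sample that is already planned, and hold randomisation until the result is known. Applying the check to every arm before allocation avoids exclusions from the VLCD arm alone.

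Narrow the closing sentence of Assessment of safety to something like: *apart from a recent eGFR, no further blood testing is needed for eligibility screening*.

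The cost is one form field, an occasional added assay on blood already being drawn, and possibly a short wait before randomisation for people without a recorded value.

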#### VLCDs

Very low calorie diets are a recognised treatment for obesity. They form part of the NICE (2006) guidelines [14] for the management of adult obesity and are advised for up to three months of continuous use in people with a BMI > 30. We are using it for 5 weeks only in people with a BMI > 25. Weekly monitoring of weight means that if BMI falls below a healthy level treatment will be discontinued. VLCDs have been used safely for many years including in people with a BMI between 25 and 30 [16]. Since 1987 they have been subject to the regulations of the Committee on Medical Aspects of Food [39]. This is an extensively researched evidence based document detailing the formulation of VLCDs to ensure safety. The product to be used in this study complies with these standards. Thus, there is every reason to expect that treatment in this trial is safe.

Participants are warned about the side-effects of VLCDs and may contact the trial team to discuss any concerns. To this end, all participants are given a card the size of a credit card with the trial team's contact details on that will allow participants to receive advice on the VLCD or to report perceived serious adverse effects and receive advice as required. They are asked to carry this card with them at all times so that it can be used to notify medical personnel of a participant's treatment and trial involvement in case of emergency. Participants will record the occurrence of side-effects of VLCDs as specified by completing a checklist. The checklist is given to the trial healthcare professional and the healthcare professional will enquire about recorded adverse events, so as to determine the severity of any adverse event and ensure that appropriate advice is given for its management (e.g. drinking appropriate amounts of water to treat symptoms of mild dehydration.) Minor adverse reactions are monitored and managed in this way. For each known side effect listed in the checklist, the trial healthcare professional will have a definition of clinical severity. Any side effect that is classified as moderate or severe is reported to and discussed with the principal investigator. A decision on stopping therapy will then be made with the participant, attending clinician, principal investigator and other relevant parties as appropriate.

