#### Smoking Cessation Interventions for all Patients

All participants have identical treatment to stop smoking. This is the treatment which is available on the NHS. It is withdrawal orientated such that behavioural strategies and nicotine replacement are given to relieve withdrawal symptoms. This has been shown to be an effective model for stopping smoking [29]. Individuals are seen over 7 consecutive weeks, weeks -3 and -2 prepare them for quitting, they quit at week 0, weeks +1, +2, +3 and +4 support them during the first 4 weeks after quitting when withdrawal symptoms are at their strongest. The sessions incorporate a variety of behavioural change techniques, pre-quit sessions prompt intent formation (technique 4) by setting a quit date, they prompt barrier identification (technique 5) and relapse prevention (technique 23) when participants identify times or places when it will be particular hard for them to resist smoking, they discuss a strategy to help them to deal with these circumstances; for example, changing routine so the usual smoking cues are removed. Quit week and the weeks that follow provide instruction (technique 8) in the use of nicotine replacement, review of and further planning of strategies (technique 11) to deal with withdrawal symptoms and general encouragement (technique 6). Self-talk (technique 22) is encouraged such that participants are asked to see and describe themselves as a 'non-smoker' and to frequently bring to mind the benefits of quitting that they are looking forward to.

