#### Training and supervision

Treatment is provided by trained practice nurses. Training is given by NHS stop smoking services (2 days), a research nurse and a general practitioner (GP) (1/2 day), and a registered dietitian (1.5 days). Nurses are given the clinical protocol to read before training sessions. Training includes explanation of dietetic and behavioural interventions and practicing the interventions on each other. The clinical protocol is clarified where needed and questions answered. The aim of the training is to equip the nurses so that, once they have completed it, they feel confident to deliver the interventions according to the clinical protocol.

After the training, 'hands on' supervision is available for the first few clinics. Immediate telephone access to the dietitian and GP is available for all clinical queries throughout the rest of the trial.

Medical history and any medication used or altered during the trial is monitored. Any significant changes in clinical condition of individual participants, as measured on a weekly basis, is discussed with the supervising GP and action taken, e.g. clinically significant fall in blood pressure in participants on the VLCD taking anti-hypertensives will require adjustment of anti-hypertensive medication. The participant's own GP is kept informed.

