#### Ketosis

The presence or absence of ketones will be measured using ketostik test strips dipped into urine samples. This will be done weekly during the first 6 weeks of dietary intervention, this is to check those in the VLCD are in ketosis throughout the five weeks and come out of ketosis during the re-feeding week. It is also measured during this time in IDAP and control arms to verify the absence of ketosis in these groups or identify any participants which might be self-imposing excessive dietary restriction, (unless undiagnosed diabetes presents itself).

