#### Dietary and Lifestyle Advice

Healthy dietary and lifestyle advice is individually tailored to create a mild energy deficit and gentle increase in activity. This advice is given by appropriately trained healthcare professionals. It is usual practice and considered very safe. In the unlikely event of side effects participants may contact the trial team to discuss any concerns. To this end, all participants are given a credit card-sized card with the trial team's contact details on that will allow participants to report perceived serious adverse effects and receive advice as required.

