#### NRT Patches

NRT has been investigated in several hundred previous clinical trials and is widely prescribed worldwide and subject to safety monitoring, and is replacing a product, nicotine, which the participants are already consuming and will have consumed for many years in cigarettes. Thus, there is every reason to expect that treatment in this trial is safe. Participants are warned about the side-effects of NRT and advised not to stop taking the medication without consulting with the trial team or an NHS professional if the trial team are unavailable. Participants will record the occurrence of side-effects of medication as specified on the summary of product characteristics (SPC) for all relevant NRT preparations, by completing a checklist. The checklist is given to the trial healthcare professional and the healthcare professional will enquire about recorded adverse events, so as to determine the severity of any adverse event and ensure that appropriate advice is given for its management (such as rotating the patch site or use of emollients for skin reactions). Minor adverse reactions are monitored and managed in this way. For each known side effect listed in the SPC, the trial healthcare professional will have a definition of clinical severity. For example, a mild skin site reaction to the patch is defined as burning sensation that does not interfere with normal activities, redness or swelling at the site of application, or mild blistering. Any reaction beyond that is classified as potentially moderate or severe and is reported to and discussed with the principal investigator. A decision on stopping therapy will then be made with the participant, attending clinician, principal investigator, and other relevant parties as appropriate. Nicotine has a short half life (2 hours), meaning that the blood concentration will not build up during the course of treatment so that new side-effects are not expected after the first few weeks. In addition, reactions to it relate to local use, such as skin discomfort from patches and people become accustomed to the side-effects after a short time of using the preparation. The advice given will depend upon the severity of the reported reaction and those with moderate reactions are invited to an ad hoc consultation.

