#### Salbutamol

Salbutamol has been thoroughly investigated in clinical trials and is widely prescribed worldwide and subject to safety monitoring. Thus, there is every reason to expect that its use in this trial is safe. Common side effects to salbutamol are mild (e.g. headache, tremor) and rare with small doses; severe reaction is very rare. Any reaction tends to be immediate. Participants are warned about the side-effects of salbutamol and asked to give verbal consent to taking it. They will take a small dose (200 mcg) in the company of healthcare professionals and given a contact number should they experience any adverse events in the hours that follow. This is administered 4 times during the year, at baseline, 12 weeks, 6months and 1 year. For each known side effect listed in the SPC, the trial healthcare professional will have a definition of clinical severity. Any reaction beyond that is classified as potentially moderate or severe and is reported to and discussed with the principal investigator. If it is felt that a person has suffered side-effects which are related to the salbutamol then they will not have the salbutamol administered next time.

The long history of use in and outside of trials for salbutamol means that SUSARs are unlikely. On the reverse of the trial card given the contact number for advice on side-effect management, there are instructions for the reporting of serious adverse events. Through direct contact from the participant or contact from their attending physician, we expect to become aware of serious adverse events. If any member of the trial team becomes aware, they will inform the principal investigator within 24 hours. The principal investigator will then assess the seriousness, causality, expectedness and severity of the adverse effects. If an event is judged severe, it is reported to the trial sponsor, who will report the event to the Research Ethics Committee (REC). Definitions of adverse events are contained in additional file 3.

Participants are asked weekly to report intercurrent illnesses and the response recorded. If any of these intercurrent illnesses contra-indicates Salbutamol, NRT, VLCD or Healthy Dietary Advice, this is immediately reported to the principal investigator and a decision made about continued use.

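### VLCD side-effects are solicited by checklist but no equivalent is described for the other diet arms, so symptoms specific to that list have no like-for-like comparator

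*Protocol article*

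**What the plan says.** The protocol article's Assessment of safety section treats each intervention under its own heading.

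- **VLCDs:** "Participants will record the occurrence of side-effects of VLCDs as specified by completing a checklist". The form goes to the healthcare professional, who asks about the events recorded on it and has a severity definition for each known side-effect. Moderate or severe items go to the principal investigator.
- **Dietary and Lifestyle Advice:** "In the unlikely event of side effects participants may contact the trial team to discuss any concerns". The means of contact is a card: "all participants are given a credit card-sized card with the trial team's contact details on". No checklist, prompted enquiry or severity definition is described here.
- **NRT Patches:** here too the method is a checklist: "Participants will record the occurrence of side-effects of medication as specified on the summary of product characteristics (SPC) for all relevant NRT preparations, by completing" (the sentence goes on to name that form). Enquiry and grading then follow as for the VLCD. Under Smoking Cessation Interventions for all Patients, "All participants have identical treatment to stop smoking", so this form applies in every arm.
- **Salbutamol:** "Participants are asked weekly to report intercurrent illnesses and the response recorded", with no restriction by arm.

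The control arm has no diet-safety text of its own. Elsewhere, Training and supervision provides for weekly review: "Any significant changes in clinical condition of individual participants, as measured on a weekly basis, is discussed with the supervising GP and action taken". Under Ketosis, urine is tested in the IDAP and control arms partly to "identify any participants which might be self-imposing excessive dietary restriction".

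**The concern.** A symptom that is prompted for and graded in one randomised arm, but recorded in another only if the participant volunteers it, will look commoner in the first arm even when its true frequency is the same. All three arms are stopping smoking on the same patch, so some symptoms will occur whatever the diet. An equally collected control rate is what would show how much of a VLCD symptom rate belongs to the diet. The trial is unblinded and is described in the Background as a small-scale model of a larger trial. An uneven collection method could be carried forward into that trial, and its side-effect rates could be used in planning it.

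**Working it through.** The plan gives no figure on this point. The sample size concerns cravings and has no bearing on it. The check is therefore a comparison of passages.

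**1. Is a difference in method stated, or is detail merely absent?** The VLCD and NRT subsections describe checklist, enquiry and grading in nearly the same terms. The Dietary and Lifestyle Advice subsection stands between them and describes participant-initiated contact instead. The article thus states two methods for two randomised diets. It does not say in so many words that only the VLCD arm completes the VLCD form, but the heading makes that the natural reading.

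**2. What is collected alike in every arm?**

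| Source in the article | What it captures | Described as covering VLCD side-effects? |
|---|---|---|
| NRT Patches | Patch side-effects from the product summary, by checklist | No |
| Measurement of urges to smoke and hunger | MPSS-C and HCS diaries, daily for the first four weeks of quitting, then weekly | No; covers withdrawal, urges, hunger and food craving |
| Salbutamol | Weekly question on intercurrent illness, used to detect contraindications | No |
| Training and supervision | Significant changes in clinical condition, weekly | No |
| Measurement of Disease Risk Factors | Weekly weight, waist/hip ratio, body fat, blood pressure, heart rate | No; physiological measures |
| Ketosis | Weekly urinary ketones | No; biochemical measure |

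**3. What is left over?** A symptom that appears on the VLCD list and also on one of these instruments has a comparator. A symptom on the VLCD list alone has none. Neither the VLCD list nor the patch list is shown, so the number of such symptoms is unknown.

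**4. Direction of the bias.** Let a symptom have the same true rate *p* in two arms, with a share *c*₁ captured in the VLCD arm and *c*₂ in the comparison arm. The apparent excess is *p* × (*c*₁ − *c*₂), which is positive whenever prompting captures more than volunteering does.

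**5. Why no size can be given.** Suppose capture by checklist is complete (*c*₁ = 1). The excess is then *p* × (1 − *c*₂). The values of *p* and *c*₂ below are assumptions; the documents supply neither.

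| True rate in both arms | *c*₂ = 80% | *c*₂ = 50% | *c*₂ = 30% |
|---|---|---|---|
| 10% | 2 points | 5 points | 7 points |
| 30% | 6 points | 15 points | 21 points |
| 50% | 10 points | 25 points | 35 points |

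For example, 30% × (1 − 0.5) = 15 points. The span from 2 to 35 points shows that the result is set by the assumptions. Because the other arms have some prompted collection, the low-capture columns may not apply at all.

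**The case against.** The case on the other side is substantial.

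- **The other arms are actively monitored.** A reader might infer that they depend wholly on participants calling in. The instruments in the first table contradict that. Contact by card is the described route for side-effects of dietary advice, not for all events.
- **VLCD effects are not inseparable from quitting and patch effects.** A reader might infer that they are. Quitting and the patch are common to all randomised arms, and withdrawal scores and patch effects are collected in the same way in each. Only symptoms outside those instruments lack a comparator.
- **No comparison of harms is planned.** A reader might infer that the primary acceptability objective is biased. The Acceptability list comprises interviews, response, recruitment, drop-out, attendance, adherence and quality of life. It contains no checklist event rates, its measures are defined alike for all arms, and the quantitative ones are to be summarised descriptively. The checklist's stated purpose is to manage side-effects, and closer watch on the more intensive diet is a defensible safety choice.
- **The ketone test is surveillance, not a prediction.** The article allows that some IDAP or control participants might over-restrict and tests for it. It does not say that it expects this.
- **The form may be specified elsewhere.** The clinical protocol and additional file 3 are not shown, and they may say that all arms complete it.

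The first four points stand and limit the concern. The fifth stands in part: the form's schedule may well be in the full protocol, but the contrast between the two diet subsections is in the article's own text.

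**Conclusion.** The point holds in a limited form. As described, VLCD side-effects are solicited and graded, those of dietary advice are left to participant contact, and control has no diet-symptom form. Symptoms on the VLCD list that no all-arm instrument covers therefore have no like-for-like comparator, and a contrast between arms would be biased towards more VLCD events. This rests on reading the VLCD checklist as confined to the VLCD arm, and on prompting capturing more than volunteering. The amount of bias cannot be estimated, and a claim that the apparent excess would be some multiple of the true one has no basis in the documents. The point does not undermine a planned analysis. It is a cheap improvement to the usefulness of the side-effect data for the later trial.

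**What to change.** State which arms complete the VLCD side-effect checklist and when. Preferably, have all three arms complete the same symptom checklist, with the same enquiry and severity definitions, at the weekly visits they already attend during the diet phase, and report each item descriptively by arm. The change concerns data collection only and alters no treatment.

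The cost is one existing form, a little nurse time, and more minor events to log in the IDAP and control arms.

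If the checklist is to remain VLCD-only, add a sentence saying that its rates describe the VLCD arm alone and are not to be compared between arms.
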